### Statistical analysis

2.11

Quantitative data will be gathered using structured questionnaires and would then be entered into Microsoft Excel for analysis. All major analyses would follow the intention-to-treat (ITT), and the per-protocol (PP) analysis would be performed for sensitivity testing. Descriptive statistics would be utilized for summarizing starting information, feasibility variables such as the number of participants, and use of the system.

For continuous data, the mean and standard deviation for normally distributed data, and the median and 25th to 75th percentiles for non-parametric data, will be presented. For comparison of groups initially untreated, and for groups measured once, independent samples t-tests and their non-parametric analogs would be employed. Categorical data would be expressed as frequency and percentage and would be analyzed using chi-squared tests. Normality of the data would be tested using the Kolmogorov Smirnov test.

Missing data will be handled using established multiple imputation methods where appropriate, under the assumption that data are missing at random. Patterns of missingness and attrition will be examined and compared between groups to identify potential differential dropout, and sensitivity analyses will be performed to compare imputed and complete-case results.

For the main trial, the focus would be on the use of the linear mixed-effects models for the evaluation of the primary outcome measures, such as the blood pressure, blood sugar, and blood fats. Additionally, the age factor would be incorporated as the covariate, which would account for the differences that people of varied ages would present, especially between the ages of 18 and 60. For secondary outcomes, such as the self-management and the psychosocial/cognitive outcomes, the analyses would use similar mixed-effects models or simpler comparative methods, depending on the nature and timing of the data collection. Also, exploratory age-stratified analyses may be conducted to descriptively examine potential heterogeneity of intervention effects across age groups, with results interpreted cautiously given the pilot nature of the study.

Measures of system use (e.g., numbers of questions) will be summarized descriptively and may be included as covariates in exploratory analyses to better understand adherence patterns; these analyses will be considered hypothesis-generating rather than confirmatory. All statistical tests will be two-tailed with a significance level of 0.05. Data analyses will be performed using IBM SPSS Statistics (version 24.0; SPSS Inc., Chicago, IL, United States) and Stata (version 14.0; StataCorp, College Station, TX, United States).

At 3, 6, and 9 months following the completion of the intervention, this study will conduct structured interviews to assess participants’ perception of the intervention as attractive, acceptable, easy to use, and satisfactory as a whole. These interviews will attempt to identify, in depth, the most prominent determinants of behavior change and engagement. Each interview should be approximately 30 min long to conduct and may be conducted over the telephone or face-to-face. Participant recruitment will take into account socio-demographic variables like residence, gender, age, education level, as well as stroke severity, to attain diverse representation. Content of interview will include participants’ own experience of the intervention, suggestions for improvement of AI-HEALS system, motivation to pursue self-management activities, as well as challenges that develop in the process. To attain richness as well as data breadth, interviews should be continued until thematic saturation has been achieved. All interviews should be audio-recorded, transcribed verbatim, as well as de-identification carried out on them. Data analysis should make use of the Theoretical Domains Framework (TDF) on NVivo 12 (Version 12, QSR International, Doncaster, Australia). Lastly, qualitative findings would be integrated with quantitative data to attain a richer understanding of the impact of the intervention as well as long-term effects on participants’ health behavior as well as outcomes.

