### Study sample

2.3

Consecutive sampling method will enroll stroke patients currently receiving treatment at a tertiary Grade A hospital of Luoyang, China, from February 2025 to February 2026. Inclusion and exclusion criteria are set as follows:

Inclusion Criteria: Patients 18 to 60 years old; Diagnosed as acute stroke based on 2019 Chinese major cerebrovascular disease diagnostic guidelines (20), with confirmation of stroke lesion by cranial CT or MRI; A score of ≤5 on the National Institutes of Health Stroke Scale (NIHSS) at the time of admission (21, 22); Patients gave their informed consent and voluntarily participated in this study.

Exclusion Criteria: Those with severe mental illness or cognitive impairment who are unable to cooperate with the researcher; those who are unable to use a smartphone; and those who have participated in related research in the past.

Withdrawal Criteria: Voluntary drop-out of the participant due to personal reasons (e.g., scheduling, loss of interest); During the research, seriousness of severe adverse events, such as severe illness or acute illness episode (e.g., myocardial infarction, serious infection), that requires the cessation of the intervention; Clinical changes or new guidelines for treatment that would necessitate alterations to the participant’s treatment regimen that may conflict with the study intervention.

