### Informed consent

2.6

Informed consent process shall be carried out openly, transparently, strictly abiding by ethic values. Patients meeting inclusion, exclusion criteria shall be given a clear, detailed, written statement of the primary objectives of the study, special procedures, potential risks as well as benefits, including data protection available to them. It shall include all explanations of how their data shall be collected, stored, secured. All data shall be saved on secure, encrypted format on specially guarded servers, readable only by authorized personnel of the research team once they are on the study, disposed of properly at study completion.

Participants will have sufficient time to read the informed consent form, pose questions, and willingly offer their written consent. They will fully be made aware of the privilege of withdrawing from the study at whatever time without adverse effects on them. The research team will offer sustained contact details to ensure that participants may, at whatever time, request further clarification or help. During the study, new information that may influence participants’ motivation to continue will, at once, be revealed, hence preserving ongoing informed consent throughout the study.

Moreover, participants will incur no penalty for choosing to withdraw from the intervention group. If the intervention has already begun, patients choosing to withdraw will never be transferred into the control group but are retained as dropouts. Semi-structured interviews, as far as possible, shall be conducted on such persons regarding reasons for terminating. During consent, participants shall be specifically informed of all post-withdrawal decisions such that at all steps they remain fully aware of decisions as well as rights of theirs that persist over time of study.

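### The one missing-data sensitivity analysis named, imputed against complete-case, cannot show whether dropout depends on unobserved outcomes; a delta-adjusted imputation should be added

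*Protocol article*

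**What the plan says.** Section 2.11 of the protocol article applies multiple imputation "under the assumption that data are missing at random". The same sentence that plans to compare attrition by arm closes with the only sensitivity analysis for missing data: "sensitivity analyses will be performed to compare imputed and complete-case results". The primary outcomes are to be analysed by mixed models ("the focus would be on the use of the linear mixed-effects models for the evaluation of the primary outcome measures"), which also rest on missing at random. A second sensitivity analysis is named, "the per-protocol (PP) analysis would be performed for sensitivity testing", but it concerns adherence and not why data are missing.

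Section 2.3 gives three grounds for withdrawal: personal reasons, with loss of interest as an example; a serious event or acute illness "that requires the cessation of the intervention"; and a change in treatment that may conflict with the intervention. Section 2.6 says of the intervention group that "patients choosing to withdraw will never be transferred into the control group but are retained as dropouts". Section 2.4 expects 20% dropout. Section 2.9.1 schedules the primary outcomes at six time points, the last 9 months after the intervention ends.

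**The concern.** A sensitivity analysis for missing data is useful when it relaxes the assumption of the main analysis. Complete-case analysis does not do that. For a missing outcome it generally needs missingness to be unrelated to that outcome given the covariates in the model. Multiple imputation needs the same given all the observed data. If people leave because of how they are doing, in a way that earlier records do not capture, both fail, and usually in the same direction. Agreement between them then says nothing about that kind of dropout, and disagreement mainly shows that missingness depends on what was observed.

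The question is live here. The illness and treatment-change criteria are tied to the intervention, so they may act mainly in one arm, and such events are plausibly linked to later blood pressure, HbA1c and lipids. If intervention-arm dropouts do worse than imputed, the benefit is overstated. Section 2.4 says the estimates from this trial will help to set the size of a larger one, and an overstated effect would leave that trial too small.

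**Working it through.** **Inputs from the protocol article.** 25 evaluable per arm, 20% dropout, 30 recruited per arm (section 2.4); 1:1 allocation (section 2.2). The recruitment target reproduces as 50 × 1.2 = 60. At 20% dropout, 0.2 × 30 = 6 leave each arm and 24 remain. The article gives no SD and no target effect, so everything below on departures from missing at random is assumed.

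**Step 1: shift in the between-arm difference.** Let d be the dropout fraction and δ the amount by which dropouts are worse than imputed, in the intervention (I) and control (C) arms:

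shift = d_I × δ_I − d_C × δ_C

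For systolic pressure with d_I = 0.2, δ_I = 5 to 10 mmHg (assumed) and δ_C = 0 (control dropouts follow missing at random): 0.2 × 5 = 1 mmHg and 0.2 × 10 = 2 mmHg.

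In SD units, so that the result carries over to HbA1c and lipids:

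| Dropout I / C | δ_I | δ_C | Shift (SD) |
|---|---|---|---|
| 20% / 20% | 0.5 | 0 | 0.10 |
| 20% / 20% | 1.0 | 0 | 0.20 |
| 20% / 20% | 0.5 or 1.0 | same as δ_I | 0 |
| 30% / 10% (assumed) | 0.5 | 0 | 0.15 |
| 30% / 10% (assumed) | 1.0 | 0 | 0.30 |
| 30% / 10% (assumed) | 0.5 | 0.5 | 0.10 |
| 30% / 10% (assumed) | 1.0 | 1.0 | 0.20 |

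The mmHg and SD ranges are separate assumptions, not conversions of each other.

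**Step 2: would the planned comparison show it?** Simulation with 30 per arm, true effect 0, one follow-up outcome, baseline-outcome correlation 0.5 (assumed) and 2000 trials per scenario. Complete-case analysis adjusted for baseline was set against within-arm regression imputation with 20 imputations. Estimates are in SD units; negative favours the intervention.

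| Dropout mechanism | Dropout I / C | Complete-case | Imputed | Mean absolute gap |
|---|---|---|---|---|
| Completely at random | 20% / 20% | 0.000 | 0.001 | 0.026 |
| At random (depends on baseline, intervention arm) | 22% / 17% | −0.004 | −0.003 | 0.034 |
| Depends on outcome, both arms alike | 21% / 21% | 0.009 | 0.009 | 0.033 |
| Depends on outcome, intervention arm only | 21% / 18% | −0.137 | −0.139 | 0.027 |
| Same, stronger | 33% / 14% | −0.309 | −0.322 | 0.039 |

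The gap between the two methods is about 0.03 to 0.04 SD in every row, whether both are unbiased or both are off by 0.3 SD. The comparison does not separate the cases.

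The simulation imputes from baseline only. With several earlier visits, imputation could recover part of the missing information and move away from the complete-case result. That would still not reveal dependence on values never observed.

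**Step 3: scale against random error.** With 24 completers per arm and an assumed systolic SD of 12 to 20 mmHg, the unadjusted standard error of the difference is SD × √(2/24): 12 × 0.289 = 3.5 and 20 × 0.289 = 5.8 mmHg. A shift of 1 to 2 mmHg is below one standard error.

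**The case against.** The strongest reply is that the article states its assumption openly and never claims that the complete-case comparison tests it. An unseen analysis plan may add an analysis that departs from missing at random. That limits the point to what section 2.11 fixes, but section 2.11 does choose a method, and the method does not serve as a check on the stated assumption.

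Second, the comparison does not stand alone: "Patterns of missingness and attrition will be examined and compared between groups to identify potential differential dropout". Section 2.9.3 records why people leave and compares them with completers, section 2.6 plans interviews on stopping, and the Discussion warns that bias may remain after imputation. A reader might infer that the plan leaves the team falsely reassured. The documents do not support that. These are, however, diagnostics and cautions; none shows how far the estimate would move.

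Third, a reader might infer that loss of interest removes people from the intervention arm only. Section 2.3 does not mention the app there, and controls can lose interest too. Serious illness can also occur in either arm, although that criterion is worded around the intervention. Nor do the documents show that missing at random is false; earlier visits may carry enough information for it to hold.

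Fourth, section 2.4 describes a pilot without power for hypothesis tests, so a search for the point at which a conclusion changes has limited meaning. This stands and shapes the remedy. It does not remove the point, because the article keeps physiological primary outcomes (section 2.9.1) and two-sided tests at 0.05 (section 2.11), and intends to use the estimates for planning.

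**Conclusion.** The point holds with moderate weight. The one missing-data sensitivity analysis that section 2.11 names cannot detect outcome-dependent dropout, because both estimates can carry the same bias. Such dropout is plausible from the withdrawal criteria but not established.

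The illustrative size is 1 to 2 mmHg systolic at the planned 20% dropout. It rests on an assumed departure of 5 to 10 mmHg in the intervention arm and on control dropouts following missing at random. It is zero if dropout and departure are equal in both arms. Larger shifts need a dropout rate or imbalance that the article does not give. The shift is small against the random error of a trial this size, but unlike random error it does not average out, and it would carry through to the effect size used for the later trial.

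**What to change.** Keep the complete-case comparison as description. Add to section 2.11, for the primary outcomes, a delta-adjusted multiple imputation:

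- Worsen the imputed values by fixed amounts in SD units, for example 0.5 and 1.0 SD, so that one rule serves blood pressure, HbA1c and the lipids. State the adverse direction for each; for HDL-C it is downward.
- Apply the deltas once to the intervention arm alone and once to both arms.
- Report how the effect estimate and its confidence interval move, not only whether significance changes.
- Optionally add one reference-based imputation, in which intervention-arm dropouts are imputed from the control arm.

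The withdrawal reasons already collected under section 2.9.3 can help to judge which deltas are credible. The cost is a short addition to section 2.11, some thought on applying the deltas across several outcomes and visits, and a little code on imputations already planned. The sensitivity result may be less favourable to the intervention.

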### Sample size

2.4

This research study was designed as a single-blind RCT. The primary objective of the study was to ensure if the AI-HEALS intervention program is feasible, acceptable, and easily implementable, as opposed to determining the efficacy of the program. Thus, it is sample size was determined based on the format for conducting a pilot study as proposed by Billingham et al. (23). Based on such recommendations, the minimum number of participants for our study would be 50, consisting of 25 per group, to ensure the objectives are achieved for the pilot study. Taking into consideration the expected dropout of 20%, the minimum number of people to recruit would be 60, 30 for each group. This sample size is expected to provide reliable estimates of feasibility parameters and preliminary effect size estimates for planning a subsequent fully powered RCT.

Although the pilot trial is not designed to have statistical power for testing hypotheses, it will provide an estimate of the average and variability in the primary outcome variables, such as blood pressure, glucose, and lipid levels. These estimates of effect size would then help design the study size for the future larger randomized clinical trial, which would be powered for testing the intervention at the conventional levels of alpha = 0.05 and 80–90% power.

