#### Primary outcomes

2.9.1

The primary outcomes of this trial are changes in key physiological parameters among patients with mild-to-moderate stroke. These include: Blood pressure, Blood glucose, Blood lipid levels. Measurements will be collected at baseline, discharge, the end of the 3-month intervention, and at 3, 6, and 9 months post-intervention. These indicators constitute the primary endpoints as they represent the main clinical effects targeted by the AI-HEALS intervention.

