In spite of the salutary possibilities of the planned intervention, there are certain limitations that must be recognized. First, the results may be limited in terms of generalizability as a consequence of the inclusion criterion, which aims at targeting a certain subgroup of the population that possesses specific clinical attributes. For instance, this research concentrates on patients suffering from mild to moderate stroke that are capable of utilizing digital health interventions, which may leave out patients that possess poor health literacy or have had little experience with technology. Secondly, while the research is anticipated to provide insightful knowledge on the effectiveness of the AI-HEALS system, there may be limitations in accounting for numerous external variables that impact patients’ perceptions about recurrence risk. Triggers from the environment, socioeconomic position, and accessibility to the services of delivering health, are all significant variables that may influence outcomes but cannot easily be controlled within real-world conditions. As a way of handling this, the study incorporates the demographic and the clinical covariates into the analyses of the study in an attempt to account for such influences, although there may still remain residual confounding that may impact the results. Finally, despite planning rigorous monitoring procedures designed to ensure data quality, there may still remain relevant issues such as participant dropouts as well as missing data that may still remain a threat to the validity of the results. The research team intends utilizing multiple imputations techniques as a way of overcoming such challenges; however, the possible bias that might arise from missing data must still remain carefully considered when interpreting the results.

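### The primary mixed models name age as their covariate but give the outcome's own baseline value no stated role, which may cost precision at 25 per arm

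*Protocol article*

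**What the plan says.** Protocol article, section 2.9.1 (Primary outcomes): "The primary outcomes of this trial are changes in key physiological parameters among patients with mild-to-moderate stroke", namely blood pressure, blood glucose and blood lipids. On timing it says: "Measurements will be collected at baseline, discharge, the end of the 3-month intervention, and at 3, 6, and 9 months post-intervention". A baseline value of each primary outcome is therefore scheduled for every participant.

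Section 2.11 (Statistical analysis) says that "the focus would be on the use of the linear mixed-effects models for the evaluation of the primary outcome measures" and adds that "the age factor would be incorporated as the covariate", giving age differences between participants as the reason. It names no other covariate for these models. It does not say whether the baseline measurement is a covariate, a response, or absent from the model.

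Section 5 (Discussion, limitations) says that "the study incorporates the demographic and the clinical covariates into the analyses of the study". Those covariates are not listed, and section 2.11 contains no clinical one.

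Section 2.4 (Sample size) sets the scale: "the minimum number of participants for our study would be 50, consisting of 25 per group". It describes an unpowered pilot meant to supply effect sizes and variability for a later trial.

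**The concern.** For a continuous outcome measured before and after randomisation, the baseline value of that outcome is usually the first covariate to consider. Section 2.11 selects and justifies one covariate and passes over this one. The Discussion then describes a wider adjustment that section 2.11 does not contain.

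Two readings of the text would be inefficient. In one, only post-baseline values are modelled, with age. In the other, baseline is the first repeated measure, arm means at baseline are free to differ, and the effect is the group-by-time contrast. That second model is the usual one and fits endpoints defined as changes, but its contrast has the variance of a change score.

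At stake is the width of the intervals around the effect estimates that the pilot exists to provide, and how far those estimates move with a chance baseline difference between small arms.

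**Working it through.** **Inputs.** 25 per arm comes from section 2.4. The baseline-outcome correlation r (given age) is not in the documents, so it is assumed and shown as a range. Equal SDs at baseline and follow-up, complete data and a single follow-up visit are also assumed. The plan states no precision figure to reproduce. Its recruitment target of 60 equals 50 × 1.2; with 20% lost, 60 × 0.8 = 48, or 24 per arm, so 25 is a fair working number.

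**Formulas.** Variance of the between-arm difference, in units of 2σ²/n:
- follow-up only, baseline ignored: 1
- change contrast, baseline an unconstrained response: 2(1 − r)
- baseline as covariate, or as response with arm means constrained equal: 1 − r²

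A generalised least squares calculation with six visits, compound symmetry and complete data gave the same values at r = 0.3, 0.5 and 0.7.

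**Direction.** This needs no value of r. Since 2(1 − r) − (1 − r²) = (1 − r)² ≥ 0 and 1 − r² ≤ 1, adjustment is asymptotically never worse than either alternative.

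**Size.** The last two columns are n × (variance ratio − 1) with n = 25.

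| r (assumed) | Change | Adjusted | Below change | Below follow-up only | Extra per arm vs change | Extra per arm vs follow-up only |
|---|---|---|---|---|---|---|
| 0.3 | 1.40 | 0.91 | 35% | 9% | 13.5 | 2.5 |
| 0.5 | 1.00 | 0.75 | 25% | 25% | 8.3 | 8.3 |
| 0.7 | 0.60 | 0.51 | 15% | 49% | 4.4 | 24.0 |
| 0.9 | 0.20 | 0.19 | 5% | 81% | 1.3 | 106.6 |

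At r = 0.5, 25/0.75 = 33.3 per arm. A one-covariate small-sample penalty of 1 + 1/(2 × 25 − 4) = 1.022 gives 25/(0.75 × 1.022) = 32.6, so the gain falls from 8.3 to about 7.6 per arm. The two comparators behave in opposite ways: the gain over the change contrast shrinks as r rises, and the gain over a follow-up-only comparison grows.

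**Chance imbalance.** The baseline difference between arms has standard error √(2/25) = 0.28 SD, so a gap above 0.3 SD in either direction has probability of about 29% for each outcome. Given a gap d, the expected shift is r·d in a follow-up-only estimate and −(1 − r)·d in a change estimate. At r = 0.5 and d = 0.3, each is 0.15 SD in size. Baseline adjustment removes this shift under a linear relation.

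**The case against.** The strongest reply is that the defect is inferred. Section 2.11 does not say that age is the only covariate and does not exclude baseline. The measurement schedule includes baseline, so a repeated-measures model may already contain it. With arm means constrained equal at baseline, the loss is zero. The clinical covariates in the Discussion could include the baseline value. The article is condensed and an SAP may exist, so time coding and covariance structure are fairly left to it. All of this stands, and it makes the loss conditional. It does not remove the point: the article chose a covariate and wrote it down, left the more useful one without a role, and describes a different covariate set in the Discussion.

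A second reply is that the trial is an unpowered pilot. That is true, and no planned power is lost. But section 2.4 makes estimation for the next trial the purpose, and precision serves that purpose.

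A third reply is that the size depends on an assumed r and an assumed comparator. That stands too. The gain is only 1 to 3 patients per arm at r of 0.8 to 0.9 against a change contrast, or at r of 0.3 or less against a follow-up-only comparison (2.5 at r = 0.3).

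Baseline availability also needs care. It is scheduled for all, but Table 1 has no row for these outcomes, section 2.10.2 places blood sampling only within the hospital stay and at follow-up visits, and section 2.11 expects missing data. A reader might infer that every participant will have a baseline value; the article supports only that one is planned.

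**Conclusion.** The point holds as a conditional one. Section 2.11 names age and gives the outcome's baseline value no stated role, and the Discussion describes adjustment that section 2.11 does not contain. If baseline is ignored or enters unconstrained, the estimate is less precise than the same data allow. At an assumed r of 0.5 the variance is a third larger than it need be (1/0.75 = 1.33) under either reading; the table in the working gives the range. If a constrained-baseline model was intended, nothing is lost and only the wording needs repair.

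A reader might infer several stronger things that the documents do not support:
- That the plan certainly throws away precision. The text leaves the model open.
- That age explains little between 18 and 60. No figure for this is given.
- That the planned estimate is biased on average. Randomisation protects against that; the exposure is to imbalance in the particular sample drawn.
- That adjustment improves the estimate of the outcome's own SD, which section 2.4 wants. It yields a residual SD, which is a different quantity, though useful for planning a baseline-adjusted trial.

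**What to change.** State in section 2.11 that each physiological outcome is analysed with age and the outcome's own baseline value, the latter interacting with time, as covariates. Alternatively, state that baseline is part of the response vector with arm means constrained equal at that visit. Either choice settles the question. Then align the covariate statement in the Discussion with section 2.11, by listing the demographic and clinical covariates meant or by limiting the statement to those in the model.

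The covariance structure and the choice of lead contrast can be left to the SAP. The cost is a sentence or two of text and about one degree of freedom per covariate term. No new data are needed.
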